## Abstract

**Background::**

Dry eye is a common ophthalmologic disorder that causes ocular discomfort and has become a worldwide health concern. Patients with dry eye often turn to complementary and alternative medicine (CAM) because of unsatisfactory conventional treatments. Acupuncture is one of the most popular interventions of CAM used, and laser acupuncture (LA) is a noninvasive technique.

**Methods::**

This protocol is a 2-center randomized controlled trial investigating the effect of laser acupuncture on dry eye. Two hundred participants aged 20 to 65 years will be randomly assigned to the experimental group (LA plus conventional treatment) or the sham control group (LA without laser output plus conventional treatment) at 2 clinical research centers in South Taiwan. The subjects will undergo LA treatment thrice a week for 12 weeks. The subjects in the experimental group will sequentially receive 0.375 J of energy at each of the following acupoints: BL2, TE23, ST2, LI4, ST36, and GB37. The subjects in the control group will also receive a sham LA treatment, without any laser output. Outcome assessments will include evaluation of the ocular surface disease index (OSDI), tear film break-up time (TFBUT), Schirmer-I test finding, and the visual analog scale (VAS) score at 4 and 12 weeks before treatment. The OSDI, TFBUT, Schirmer-I test result, and VAS score of the participants will be analyzed and compared between the experimental and control groups using the paired *t* test and one-way analysis of variance.

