### Study design

2.2

This 2-center, randomized, controlled trial is being conducted at the Department of Ophthalmology, Chinese Medicine at the Kaohsiung Chang Gung Memorial Hospital and the Sunming Eye Clinic, 2 clinical research centers in South Taiwan from August 2016 and will continue until July 2018. The participants independently recruited by each center will be randomly allocated to the experimental group (LA plus conventional treatment, n = 100) or the sham control group (LA without laser output plus conventional treatment, n = 100). All participants will receive 36 sessions of treatment over a 12-week period. The study design is depicted in Fig. 1.

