### Sample size and randomization

2.4

The necessary sample size was calculated from the results of a previous study on the effects of acupuncture. The mean difference (standard deviation) of the OSDI after acupuncture treatment was –17.61 (15.61), and after sham acupuncture, was –17.20 (18.81).^[11]^ Anticipating a 15% dropout rate, a total of 200 participants (http://powerandsamplesize.com) were recruited and evenly assigned to each center (100 participants in each center). Participants were randomly allocated to either an experimental or a sham control group using a research randomizer (https://www.randomizer.org). We equally randomized patients who were refractory to conventional treatment and those who were stable and responded to conventional treatment. The trial participants, outcome assessors, and data analysts will be blinded after assignment to interventions using label A and B for the 2 groups.

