### Outcome measurements

2.6

Both eyes will be assessed for outcomes, 4 and 12 weeks after the first visit. Outcome measurements include 2 aspects, subjective ophthalmologic tests and objective questionnaires for ocular symptoms related to dry eyes. The primary outcome is the difference in the OSDI changes between the 2 groups. The secondary outcomes are the differences in TFBUT, Schirmer I test (with anesthesia) score, and 10-cm visual analog scale (VAS) score of eye discomfort.

OSDI is a 12-item scale for the assessment of symptoms related to dry eye disease and their effects on vision.^[17]^ The scores range from 0 to 100, and higher scores represent a more severe dry eye state. TFBUT measures the time required for tears to evaporate and diffuse after blinking naturally.^[18]^ A Schirmer I test (with anesthesia) is used to assess how quickly the eyes produce tears.^[19]^ A 10-cm VAS (0–10 points, least to greatest discomfort intensity) is used to measure the intensity of eye discomfort. The OSDI and VAS score are assessed by separate outcome assessors who did not perform the LA treatment. TFBUT and Schrmir I test outcomes are evaluated by ophthalmologists.

The reasons for patients not completing the follow-up visits or dropping out of the study, such as adverse events/intercurrent illnesses, suboptimal response to therapy, failure to return for follow-up visits, failure to meet selection criteria at entry, other protocol violations, and refusal to receive treatment, will be recorded. The potential adverse events will also be recorded despite the fact that only 0.375 J will be delivered to an acupoint.

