### Statistical analysis

2.7

All data will be presented as mean ± standard deviation. The independent *t* test and chi-square test are used to evaluate and compare the baseline patient characteristics between the experimental and sham groups. Repeated measure analysis of variance and multiple comparisons are used to evaluate the changes in the OSDI, TFBUT, Schirmer I test result, and VAS score between the experimental and sham groups. Differences are considered to be significant at a *P* value of <.05. All analyses are performed with the SPSS for Windows, version 22 (Statistics 22, SPSS, IBM Corp., Chicago, IL).

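### The abstract and section 2.7 name different tests for the same outcomes, and the abstract's paired t test cannot compare two independently randomised arms

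*Protocol article*

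**What the plan says.** The Methods paragraph of the abstract lists OSDI, TFBUT, Schirmer-I and VAS and says that they will be "compared between the experimental and control groups using the paired *t* test and one-way analysis of variance".

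Section 2.7 (Statistical analysis) gives a different method for the same four measures: "Repeated measure analysis of variance and multiple comparisons are used to evaluate the changes in the OSDI", continuing with the other three outcomes and specifying that the comparison is between the experimental and sham groups. The only t test in that section is the independent one, and it is kept for baseline: "The independent *t* test and chi-square test are used to evaluate and compare the baseline patient characteristics between the experimental and sham groups".

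Two other sections fix what the analysis has to answer. Section 2.2 describes a parallel design in which participants "will be randomly allocated to the experimental group (LA plus conventional treatment, n = 100) or the sham control group", the latter also with 100 participants. Section 2.6 defines the target: "The primary outcome is the difference in the OSDI changes between the 2 groups".

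**The concern.** An abstract may shorten a method, but this one names other tests. One-way ANOVA and repeated-measures ANOVA are different analyses, and a paired t test is neither of them.

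The paired t test is also unsuited to the purpose the abstract gives it. It needs observations that come in pairs. The arms are separately randomised and the article describes no matching of patients across them. The only pairs available are a patient's own scores before and during treatment. Used on those, the test asks whether an arm changed. It does not ask whether the arms changed by different amounts.

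The stake is the meaning of a significant result. Change within an arm contains natural course, conventional treatment and placebo response as well as any effect of the laser. A report following the abstract's wording could present a within-arm p value where the primary outcome calls for a between-arm one.

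**Working it through.** **Texts side by side**

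| Place | Outcomes | Test named |
|---|---|---|
| Abstract, Methods | OSDI, TFBUT, Schirmer-I, VAS | Paired t test, one-way ANOVA |
| Section 2.7 | OSDI, TFBUT, Schirmer I, VAS | Repeated-measures ANOVA, multiple comparisons |
| Section 2.7 | Baseline characteristics | Independent t test, chi-square test |

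No outcome analysis appears in both places.

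**Inputs for the illustration**

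- OSDI change, from the earlier acupuncture study cited in section 2.4: acupuncture -17.61 (SD 15.61), sham -17.20 (SD 18.81).
- Section 2.4: "Anticipating a 15% dropout rate, a total of 200 participants". With 100 per arm, 100 × 0.85 = 85 evaluable per arm, assuming equal dropout.
- Section 2.7: "Differences are considered to be significant at a *P* value of <.05". Sidedness is not stated; two-sided is assumed.

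The article gives no result for these tests, so there is no stated figure to reproduce here. The sample size of 200 does not follow from a difference of 0.41 points, but that is a separate matter and nothing below depends on it.

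**Step 1. Paired test within each arm**, t = mean change / (SD/√n), n = 85:

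- Sham: SE = 18.81/√85 = 2.040; |t| = 17.20/2.040 = 8.43, p about 8 × 10⁻¹³.
- Active: SE = 15.61/√85 = 1.693; |t| = 17.61/1.693 = 10.40, p about 9 × 10⁻¹⁷.

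**Step 2. Between-arm test of the changes**, t = difference / √(SE₁² + SE₂²):

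- Difference = -17.61 - (-17.20) = -0.41.
- SE = √(1.693² + 2.040²) = 2.651.
- |t| = 0.41/2.651 = 0.15, p = 0.88.

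Without dropout (n = 100 per arm) the values are 9.14 for sham, 11.28 for active treatment and 0.17 between arms (p = 0.87).

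**Step 3. No laser effect at all.** In 20,000 simulated trials, both arms had a true change of -17.20 (SD 18.81) with 85 patients each. The paired test was significant in each arm in 100% of trials. The between-arm test was significant in 5.1%, which is its nominal error rate.

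**Step 4. Dependence on the assumed sham response.** With 84 degrees of freedom the two-sided 5% critical value is 1.989. At the same SD, the sham arm's paired test becomes significant once the mean change exceeds 1.989 × 2.040 = 4.06 points, less than a quarter of 17.20 (4.06/17.20 = 0.24).

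**The case against.** The best defence is that the rest of the article is clear about the target. Section 2.6 defines a between-group outcome, section 2.7 evaluates changes between the groups with a defensible method, and even the abstract says the comparison is between groups. The same abstract paragraph places the week 4 and week 12 assessments before treatment, while section 2.6 places them after the first visit. This points to careless drafting of the abstract rather than a second plan. That is a fair reading of how the conflict arose, but the published text still names two sets of tests for the primary outcome.

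Several stronger conclusions are tempting, and the article does not support them:

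- *That two rival primary analyses are prespecified.* Neither place labels a primary analysis. Both simply cover OSDI, the primary outcome.
- *That the plan would declare sham effective.* This needs the paired test to be run within arms, its result to be taken as the efficacy finding, and the sham arm to respond as in the earlier study. The article states none of these.
- *That the abstract offers no valid between-arm test.* One-way ANOVA of change scores, or of scores at one visit, is valid with two arms and equals the independent t test (here F = 0.155² = 0.02, p = 0.88). It would be wrong only if applied across visits as though these were independent, which the abstract does not say.
- *That regression to the mean explains the OSDI change.* The numerical entry cut-offs in section 2.3 are on TFBUT and Schirmer. No OSDI cut-off is given, so the argument is only indirect for OSDI.
- *That low between-arm power on the planning figures measures the harm.* That power reflects the 0.41-point planning difference and would be the same for any correct test.

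**Conclusion.** The point holds as a contradiction in the named tests and as a misuse of one of them. The paired t test is wrong for the between-group comparison the abstract assigns to it. One-way ANOVA can be a valid comparison, but it is not the analysis in section 2.7.

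On the planning figures, the gap between the two questions is |t| = 8.43 and 10.40 within arms against 0.15 between them. These values assume responses like those of the earlier study, about 85 evaluable patients per arm and two-sided testing. They show that within-arm significance carries no information on laser versus sham; they do not predict this trial's result. The contradiction itself rests on no assumption.

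**What to change.** Delete the paired t test and one-way ANOVA from the abstract. State the same single between-arm analysis of OSDI change in the abstract and in section 2.7. Two choices would serve:

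- the group-by-time contrast of the repeated-measures model at a prespecified visit; or
- a comparison of the arms at that visit adjusted for baseline OSDI.

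The first stays closest to section 2.7; the second is an acceptable alternative, not a requirement. Add one sentence saying that within-arm changes are descriptive only and support no conclusion on efficacy.

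The cost is wording in two places, with no new data, visits or patients.

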**Objectives::**

The aim of this protocol is to investigate the efficacy of LA therapy in patients with dry eye.

**Trial registration::**

ClinicalTrials.gov NCT03204903.

## Introduction

1

Dry eye or the dysfunctional tear syndrome (DTS) is a multifactorial disease characterized by a poor production of tears, leading to a dry ocular surface. Symptoms of dry eye include visual disturbance and tear film instability with potential damage to the ocular surface. The 2 major causes of dry eye are aqueous deficiency and increased evaporation.^[1]^ The global prevalence of dry eye ranges from 5% to 35% and therefore, has become a worldwide health concern.^[1,2]^ It is more common in those aged >50 years and affects mainly women (70%), and causes significant loss of productivity at work, as there is no effective therapy.^[1]^

Diagnosis and management of DTS are often challenging and a source of frustration for eye care professionals and patients with this condition.^[3,4]^ Artificial tears, gels, ointments, and inserts are used to replenish the tear film.^[5]^ However, such treatments are often palliative and inadequate in providing satisfactory relief from debilitating symptoms.^[6]^ Patients with dry eye, therefore, often turn to complementary and alternative medicine (CAM). Acupuncture therapy is one of the most popular forms of CAM, which is used for the treatment of a variety of conditions.^[7]^ While some recent studies have suggested that acupuncture could be effective for dry eye,^[8–10]^ others have failed to reach a consensus regarding the most effective acupuncture treatment method, owing to low methodological quality and insufficient sample sizes and therapeutic sessions.^[11,12]^

Acupuncture is one of the most popular interventions of CAM used. Laser acupuncture (LA) is a noninvasive technique that involves stimulation of traditional acupoints with low-intensity, non-thermal laser irradiation. LA has been used for the treatment of several eye conditions including amblyopia.^[13,14]^ LA integrates the positive effects of both acupuncture and low-level laser therapy.^[15]^ The aim of this study is to investigate the effects of LA on dry eye, based on the traditional Chinese medicine (TCM) theory, which advocates treatment of the body acupoints to replenish the tear film.

## Methods

2

### Ethics approval

2.1

The study was approved by the Human Ethics Committee of our hospital (Chang Gung Medical Foundation Institutional Review Board, IRB No. 201600333A3). The protocol was registered with ClinicalTrials.gov (Identifier: NCT03204903). Written informed consent will be obtained from all of the participants. Personal information about potential and enrolled participants will be collected, shared, and maintained in an independent closet in order to protect confidentiality before, during, and after the trial.

### Study design

2.2

This 2-center, randomized, controlled trial is being conducted at the Department of Ophthalmology, Chinese Medicine at the Kaohsiung Chang Gung Memorial Hospital and the Sunming Eye Clinic, 2 clinical research centers in South Taiwan from August 2016 and will continue until July 2018. The participants independently recruited by each center will be randomly allocated to the experimental group (LA plus conventional treatment, n = 100) or the sham control group (LA without laser output plus conventional treatment, n = 100). All participants will receive 36 sessions of treatment over a 12-week period. The study design is depicted in Fig. 1.

**Figure 1 F1:**
[figure not shown]
The flowchart of the trial.

### Participants

2.3

Diagnosis of dry eye is established on the basis of patient symptoms, assessed using the ocular surface disease index (OSDI) questionnaire, as well as visual disturbance (blurred vision or poor vision) or visual function (problems reading, driving at night, working on a computer, or watching TV) assessment; tear film break-up time (TFBUT) measurement and Schirmer test for assessing tear film stability; ocular surface staining; Optikgerate keratograph for assessing ocular/conjunctival redness; and interferometry using the LipiView II Ocular Surface Interferometer (TearScience, Inc., Morrisville, NC) device for assessing Meibomian gland dysfunction.

Patients aged 20 to 65 years with aggravating acute or chronic dry eye symptoms in one or both eyes were recruited. Physicians and ophthalmologists assessed the participants’ eligibility to participate in the study. The inclusion criteria were based on the following ophthalmologic test results: a TFBUT below 10 seconds and a Schirmer I test (with anesthesia) value below 5 mm/5 min. These tests were administered by ophthalmologists who had no information about the allocation results. Participants with eye lesions, diabetes mellitus, vitamin A deficiency, sequelae of Bell's palsy, a critical illness such as the Stevens–Johnson syndrome, cancer, infectious disease of the skin, a history of seizure or epilepsy; those who had undergone an eye operation in the past 3 months or had undergone hemodialysis; those using a combination of other ophthalmic medications, contact lens, a pacemaker, or immunosuppressants; those who had taken or needed active treatment (including Chinese medicine); and those who did not meet the physician's assessment for recruitment or was unwilling to provide informed consent were excluded. In addition, pregnant women were excluded.

### Sample size and randomization

2.4

The necessary sample size was calculated from the results of a previous study on the effects of acupuncture. The mean difference (standard deviation) of the OSDI after acupuncture treatment was –17.61 (15.61), and after sham acupuncture, was –17.20 (18.81).^[11]^ Anticipating a 15% dropout rate, a total of 200 participants (http://powerandsamplesize.com) were recruited and evenly assigned to each center (100 participants in each center). Participants were randomly allocated to either an experimental or a sham control group using a research randomizer (https://www.randomizer.org). We equally randomized patients who were refractory to conventional treatment and those who were stable and responded to conventional treatment. The trial participants, outcome assessors, and data analysts will be blinded after assignment to interventions using label A and B for the 2 groups.

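### The sample size of 200 does not follow from the OSDI changes it is said to rest on: they differ by 0.41 points, which would need about 27,900 patients per arm

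*Protocol article*

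**What the plan says.** Section 2.4 (Sample size and randomization) states where the number comes from: "The necessary sample size was calculated from the results of a previous study on the effects of acupuncture". The only results it then gives are these: "The mean difference (standard deviation) of the OSDI after acupuncture treatment was –17.61 (15.61), and after sham acupuncture, was –17.20 (18.81"). The sentence that follows gives the total: "Anticipating a 15% dropout rate, a total of 200 participants", with a pointer to an online calculator.

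Section 2.6 (Outcome measurements) fixes the contrast to be powered: "The primary outcome is the difference in the OSDI changes between the 2 groups". It also gives the OSDI range as 0 to 100. Section 2.2 (Study design) sets equal groups of 100. Section 2.7 (Statistical analysis) gives the significance level: "Differences are considered to be significant at a *P* value of <.05". The article states no target difference, power, sidedness or margin.

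**The concern.** The section names a source, prints that source's means and SDs for both arms, and presents 200 as the result. A reader will take the difference between the two printed means as the effect the trial was sized on, because that is the primary contrast. That difference is almost zero, and a trial of 200 could not be planned on it.

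At stake is the justification of the trial's size for its primary outcome. As the section stands, a reader cannot tell which difference the trial was sized to detect. Taken at face value, the cited evidence points to a near-null effect.

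**Working it through.** **Inputs from the article**
- Mean OSDI change (SD): −17.61 (15.61) with acupuncture and −17.20 (18.81) with sham (section 2.4).
- Dropout 15%, total 200 (section 2.4); 100 per group (section 2.2).
- Significance level 0.05 (section 2.7).

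**Assumptions, because the article does not give them**
- Two-sided test; one-sided also tried.
- 80% power; 90% also tried.
- A simple two-group comparison of change.

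**1. The plan's own figure.** 200 × (1 − 0.15) = 170 evaluable, or 85 per arm. A calculation that ends at 200 should therefore yield about 85 per arm before dropout.

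**2. Effect implied by the printed means.**
- Difference = 17.61 − 17.20 = 0.41 points.
- Pooled SD = √[(15.61² + 18.81²)/2] = √[(243.67 + 353.82)/2] = 17.28.
- Standardised difference = 0.41/17.28 = 0.024.

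**3. Patients needed for 0.41 points.** n per arm = (z₁₋α/₂ + z₁₋β)² × (SD₁² + SD₂²)/Δ².
- 80% power: (1.960 + 0.842)² × 597.49/0.1681 = 27,898 per arm. That is 55,796 evaluable, or 55,796/0.85 = 65,643 randomised.
- 90% power: 37,348 per arm.
- Across either SD or the pooled SD, one- or two-sided tests, and 80% or 90% power, the total before dropout runs from 35,850 to 88,464. No variant is near 170.

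**4. Power of the stated size for 0.41 points** (noncentral t, two-sided 5%, pooled SD). It is 5.3% with 85 per arm and 5.3% with 100 per arm, barely above the type I error rate. A one-sided 5% test gives about 7%.

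**5. One group's change taken as the effect.**
- As a between-group difference of 17.61 or 17.20 with SD 17.28, n is 16 per arm at 80% power and 21 or 22 at 90%. After dropout the total is 38 to 52.
- As a within-group paired test at 80% power, 9 patients (active figures) or 12 (sham figures) suffice.

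These are as far below 200 as step 3 is above it.

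**6. What 85 per arm does deliver.** Detectable difference ≈ (z₁₋α/₂ + z₁₋β) × SD × √(2/n).
- 80% power: 2.802 × 17.28 × √(2/85) = 7.43 points (7.47 with the t distribution).
- 90% power: 8.59 points (8.64 with the t distribution).
- 95% CI half-width for the group difference: about ±5.2 points.

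The detectable differences are about 18 to 21 times the 0.41 points implied by the printed means.

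**The case against.** The strongest defence is that section 2.4 never calls 0.41 the target. The earlier study may have supplied only the variability, with the target difference left to the full protocol that this article condenses. Step 6 shows that this fits: with the quoted SDs, 85 per arm is what an unstated target of about 7.5 points (80% power) or 8.6 points (90% power) would require. So a reader who infers that no calculation could give 200 goes too far. The absence of power, sidedness and target difference from a journal article is also no finding in itself.

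What this does not rescue is the text as written. It says the size was calculated from the study's results, prints both means, and names no other difference. A fuller document could add the missing target, but it could not make 0.41 points yield 200. A non-inferiority or equivalence margin of roughly 7 to 9 points would also fit the number. The article states no such margin, though, and the sham control, the tests for difference and the expectation of benefit in the Discussion all point to superiority.

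Two further inferences are tempting. One is that the trial has 5% power. That figure applies only to a true difference of 0.41 points and says nothing about power for a larger effect. The other is that a null result could not be interpreted. It could be, from its confidence interval: the expected half-width is about 5.2 points, whatever the planning text says.

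**Conclusion.** The concern holds in a limited form. The printed means cannot be the planning effect behind 200. Read as the primary contrast they call for about 27,900 evaluable patients per arm, against 85 available; read as one group's change they call for a few dozen in total. Section 2.4 therefore misdescribes its basis, which goes beyond leaving detail out. The mismatch does not depend on the assumed power or sidedness, since every two-group variant for 0.41 points needs at least 35,850 evaluable patients.

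The documents do not show that 200 is the wrong number or that the trial is too small for a worthwhile effect. The detectable difference of about 7.5 points assumes that the earlier study's SDs carry over to this trial, a two-sided 5% test, 15% dropout and a simple comparison of change. Section 2.7 plans a repeated-measures analysis of variance, so the figure is a guide to that analysis and not an exact property of it.

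**What to change.** Keep 200 and correct section 2.4.

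- Remove the implication that 200 follows from −17.61 versus −17.20.
- If the inputs entered in the online calculator can be recovered, report them: target difference, SD, power and sidedness.
- If they cannot, say that the earlier study was used for the SD only (about 17.3). State that 170 evaluable patients give 80% power for a between-group difference of about 7.5 OSDI points, and 90% power for about 8.6, at two-sided 5% in a simple two-group comparison.
- Label that figure as the detectable difference. Section 2.4 already describes recruitment in the past tense, so naming 7.5 as a target now would present an after-the-fact figure as a prospective choice.
- Say whether a difference of that size is clinically worthwhile.

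The cost is a rewording of one section, with no extra patients and no change to the design, outcome or analysis. The downside is a less favourable justification: it will show openly that the trial can detect only differences far larger than the one seen in the study it cites.
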